### 3.2 CLINICAL DATA

For many years, antipsychotics and noradrenergic agents were considered the first line treatment for tics. Although there is randomised controlled trial (RCT) evidence of short-term effectiveness of these drugs for treating tics, these drugs are often associated with significant adverse effects [16], and now current European guidelines are recommending the use of BT as first-line treatment for tics in a stepped-care approach [3].

The effectiveness of BT for reducing tics has been well established [1], with systematic reviews demonstrating a similar magnitude of effect for BT compared to pharmaceutical interventions [1, 4]. Commonly used interventions include: *habit reversal training (HRT)*, where patients are taught to implement an action referred to as a competing response when a premonitory urge to tic is experienced; *exposure and response prevention (ERP)*, where patients practice to tolerate premonitory urge sensations and suppress their tics. The largest trial used a program referred to as *comprehensive behavioural intervention for tics (CBIT)*, which includes HRT and adds additional elements of relaxation training, functional analyses (identification of situations which could exacerbate tics) and social support[17]. A meta-analysis conducted by Hollis et al. showed clear evidence of effectiveness for treatment with HRT/CBIT for tics [1]. Additionally, although less studies have evaluated ERP, the evidence from available studies suggest both HRT and ERP may be equally effective in reducing tics[3]. An important benefit of BT is further the low occurrence of side effects (compared to medication).

Although BT is a recommended treatment for tics, there are a lack of trained therapists across many European countries, including Sweden, leaving many patients unable to access these treatments. A survey of 295 parents of children with TD identified that many families felt healthcare professionals were not knowledgeable about TD. Specifically, respondents noted the struggle to access limited BT resources, with 76% of parents saying they would want BT to be available for their child, highlighting the need for improved access to BT for TD.[7]

Across diagnostic conditions, studies have shown efficacy of ICBT compared to no-treatment as well as face-to-face treatment control conditions [18, 19], with an estimation of up to 50% in cost savings [19]. Therapist guidance during ICBT has been shown to be an important contributing factor to determining outcome. Although self-guided ICBT is superficially attractive, given the very low costs of implementation, research evidence demonstrates very low adherence rates, with therapist-guided ICBT having significantly greater clinical- and cost-effectiveness [20, 21].

There are some clinical data to support the use of our BIP platform (therapist guided ICBT for young people and their parents). An RCT comparing ICBT and a waiting list control in adolescents with OCD, found a significant reduction in OCD symptoms 3-months post-treatment [22]. Additionally, there were no reported adverse events, and participants were generally satisfied with the format of treatment. Symptom reduction was also noted in an RCT using the BIP platform for anxiety [23], as well as in a pilot trial using BIP for specific phobia [24]. These findings together support the use of therapist guided ICBT delivered via the BIP platform.

There is little research evidence regarding the effectiveness of ICBT and TD. In a recent review of digital health interventions, Hollis et al. found that the majority of interventions have been designed to help children and young people at risk for developing, or with a diagnosis of an anxiety disorder and/or depression, with areas such as TD being largely overlooked [25]. Some evidence is available though, including two pilot RCTs comparing videoconference delivered CBIT (e.g. Skype) to traditional face-to-face delivery in children with TD. Results showed significant tic reduction for both groups, with no difference between the modes of delivery [26, 27]. The method of delivering CBIT was rated as highly acceptable by the participants [26].

Delivering BT via videoconference might solve the long travel distances, but still demands the same amount of specialist therapists (providing the treatment in real time). Following the success of previous ICBT trials using the BIP platform, our team decided to develop BIP TIC: a therapist-guided internet-delivered behavioural intervention for young people with TD, and to evaluate its feasibility in a pilot randomised controlled trial [15]. In this trial, we randomised 23 participants aged 8-16 years to receive either therapist-guided internet-delivered HRT (called BIP TIC HRT) or therapist-guided internet-delivered ERP (called BIP TIC ERP). Participants in both groups showed improvement 3-months after treatment completion, but only participants in the BIP TIC ERP arm showed significantly reduced tic severity, as measured by the primary outcome measure Total Tic Severity Score, of the Yale Global Tic Severity Scale (YGTSS). Although not a fully powered-trial, the findings show that BIP TIC ERP may be effective in reducing tics. Furthermore, we found no severe adverse events. There were no drop-outs and no data loss at any of the assessment points, and 83% of parents and children rated the treatment as *good* or *very good*, indicating the trial was highly acceptable. Therapist time (consisting of e-mail contact within the BIP platform, and occasional phone calls) was about 25 minutes per patient and week, considerably less than the traditional weekly 60-minute-session in face-to-face or videoconference BT. In conclusion, the results showed that it is feasible to remotely deliver a behavioural intervention for TD via the internet, with high patient and parent satisfaction, requiring only minimal therapist time (making it potentially more available and cost-effective than videoconference delivered BT).

## 4 OBJECTIVES

### 4.1 PRIMARY AND SECONDARY OBJECTIVES

#### Primary:

1. To determine the clinical efficacy of BIP TIC (ERP-version) for reducing tic severity (as measured by the YGTSS Total Tic Severity Score [28]) in children and adolescents with TD and Persistent (Chronic) Motor or Vocal Tic Disorder, compared with an active control intervention (therapist- and parent-guided internet-delivered education on tics). The primary endpoint is the follow-up 3 months post-treatment.

#### Secondary:

2. To establish the 12-month durability of the treatment effects.
3. To conduct a health-economic evaluation of BIP TIC (ERP-version), compared with therapist- and parent-guided internet-delivered education on tics, from multiple perspectives, both in the short term (primary endpoint) and the long term (12-month follow-up).

## 5 PROJECT DESCRIPTION

### 5.1 DESIGN

A parallel-group, single blind, randomised controlled superiority trial for children and adolescents with TD or Persistent (Chronic) Motor or Vocal Tic Disorder. Participants will be randomised to receive 10 weeks of BIP TIC (therapist- and parent-guided internet-delivered behaviour therapy) or an active control condition (therapist- and parent-guided internet-delivered education on tics). The control condition aims to control for online access to basic information on tics, online therapist support, and homework assignments.

The default treatment length is 10 weeks, but if certain reasons (e.g. illness or holidays) the design allows participants to pause their therapist-support for a maximum of two weeks, which extends the treatment length to a maximum of 12 weeks.

Participants will be followed-up at mid-treatment, post-treatment, and follow-ups 3, 6 and 12 months post-treatment. The post-treatment and 3-month follow-up are “intention-to-treat” assessment points, where participants are encouraged not to change medication or start alternative psychological treatment for their tics. The 6- and 12-month follow-ups are naturalistic follow-ups, participants may be using alternative treatments in accordance to standard practice recommended by their usual treating clinician. Assessors will be blind to treatment allocation at all assessment points. A flow chart of the trial design is shown in **Figure 1**.

**Figure 1.** CONSORT flow diagram.

[figure not shown]

## 5.2 STUDY SITES

The project is a collaboration between the Department of Clinical Neuroscience at Karolinska Institutet and the Child and Adolescent Mental Health Service (Barn- och ungdomspsykiatri; BUP) in Stockholm.

All assessments and delivery of treatment will be administrated from a single site in Stockholm, the CAP Research Center, at [name]. Participants will formally be considered as patients at the clinic *BUP Klinisk forskningsenhet (KFE)* within BUP Stockholm,

Stockholm läns landsting, from enrolment to the 12-month follow-up. Several collaborating counties across Sweden will assist on referring potential participants to the Stockholm site for inclusion in the trial. Swedish county councils that have, to date, agreed to participate as recruitment sites are (names of key collaborators in brackets): Region Gävleborg ([name]), Västra Götalandsregionen ([name]/[name]), Västerbottens läns landsting ([name]), Landstinget Västmanland ([name]), Region Jämtland Härjedalen ([name]), Landstinget Dalarna ([name]), Region Skåne ([name]) and Landstinget Västernorrland. Additional counties will be invited to participate as the study progresses, with the aim to have full national coverage.

### 5.3 POWER ANALYSIS

Due to our primary and secondary outcome variables being integer-valued (ordinal) in nature, we estimated the power for the difference in *median* outcome between the two treatment groups at the primary endpoint using data from our pilot trial [15]. Specifically, we used a Wald test for the coefficient of the interaction term in a linear quantile random intercept model for the median of the outcome [29-31]. The model contained the intercept, the binary treatment indicator (BIP TIC, control condition), the numeric time variable (baseline, post-treatment, 3-month follow-up), and the treatment-by-time interaction term. We calculated the power under different samples sizes and differences in median outcome between the two treatment groups at the primary endpoint. For each combination of sample size and difference, we simulated 500 samples under a random intercept model with normal intercept and normal residual error. The regression parameters and variance components were obtained from our pilot data. The regression coefficients were 28.56 for the intercept, and – 3.11 for time, while the standard deviation of the random intercept was 2.95, and that of the residual was 2.04. These calculations showed that with 200 patients (100 in each arm) we would have 97% power to detect a statistically significant difference in medians of 3 points on the YGTSS Total Tic Severity Score at the primary endpoint. Allowing for a 10% dropout rate, this trial will aim to recruit up to 220 participants.

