## Appendix

### 4.7 Primary outcome analysis (objective #1)

The primary outcome is tic severity, as measured by the YGTSS-TTSS, at the primary endpoint (3FU). The primary outcome analysis (objective #1) will be based on all available data up to this time point and conducted according to the intention-to-treat (ITT) principle.

As the YGTSS-TTSS is a composite measure resulting in an integer-valued variable ranging from 0 to 50, statistical modelling will focus on the median of the outcome (i.e., the 0.5-quantile) rather than its mean. Specifically, all the randomised participants will be included to estimate a linear quantile mixed model [6-8], taking into account individual differences in pre-treatment symptomatic status and treatment response. The model will include fixed effects for time (the YGTSS-TTSS at baseline, post-treatment, and 3-month follow-up) and subject-specific effects as a random intercept factor to account for the variances between and within participants. Linear quantile mixed models use all available data, can account for correlation between repeated measurements on the same subject, can flexibly model time effects, and can handle missing data.

To enable comparisons with previous trials within the field, which traditionally have used regression models based on means rather than medians, we will also perform complementary analyses of the primary outcome measure at the primary endpoint using a linear mixed model (estimating a difference in means). Similar to the linear quantile mixed model, the linear mixed model will include fixed effects of time (the YGTSS-TTSS at baseline, post-treatment, and 3-month follow-up) and subject effects as a random intercept factor to account for the variances between and within participants. Like linear quantile mixed models, linear mixed-effects models use all available data, can account for correlation between repeated measurements on the same subject, can flexibly model time effects, and can handle missing data. Results from the linear mixed-effects model will be presented as a complementary analysis to the linear quantile mixed model.

The estimated treatment effect will be reported with the accompanying 95% confidence interval (CI) and *p*-value. The alpha level of 0.05 will be used as the threshold for statistical significance throughout all trial analyses.

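### Protocol 5.3 reports 97% power for a 3-point median difference, but with equal arms at baseline its printed inputs give above 99.9%; about 97% belongs to roughly 2 points of differential change

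*Combined protocol and SAP*

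**What the plan says.** Protocol section 5.3 bases the sample size on simulation. The test is a "Wald test for the coefficient of the interaction term in a linear quantile random intercept model for the median of the outcome". Time enters as a numeric variable over three assessments: baseline, post-treatment and 3-month follow-up. For each scenario, "we simulated 500 samples under a random intercept model with normal intercept and normal residual error". The parameters are said to come from the pilot trial: "The regression coefficients were 28.56 for the intercept", with a time coefficient of -3.11, and "the standard deviation of the random intercept was 2.95, and that of the residual was 2.04". The result reported for the primary outcome at the primary endpoint reads: "with 200 patients (100 in each arm) we would have 97% power to detect a statistically significant difference in medians of 3 points". The target of 220 adds an allowance for 10% dropout.

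Section 5.3 gives no codes for the time variable, no value for the interaction coefficient, no treatment main effect and no sidedness. The significance level comes from SAP section 4.7: "The alpha level of 0.05 will be used as the threshold for statistical significance throughout all trial analyses". Allocation is 1:1 (protocol section 6.2).

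**The concern.** The random intercept largely drops out of a treatment-by-time interaction, because each participant is compared with himself or herself over time. The residual SD therefore drives the precision. A residual SD of 2.04 with 100 per arm is very precise relative to 3 points, and one would expect power close to 100%. A reported 97% suggests that the effect, an SD or the coding used in the simulation differs from what the paragraph conveys.

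At stake is the planning statement for the primary endpoint. A reader who uses section 5.3 to judge what the trial could detect would take the difference detectable with 97% power to be 3 points. On the printed SDs it is about one point smaller.

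**Working it through.** **Inputs.** Residual SD 2.04, random-intercept SD 2.95, 100 per arm, three assessments, 3-point difference and 500 simulated samples (protocol 5.3); alpha 0.05 (SAP 4.7). Assumptions: two-sided test, time coded 0, 1, 2, and arms equal at baseline. The intercept (28.56) and time coefficient (-3.11) do not affect power.

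**1. Standard error of the interaction slope.** With codes 0, 1, 2 the sum of squares of time about its mean is 2.
- Mean model: SE = (2.04/√2) × √(2/100) = 0.204.
- Median model, using the normal-theory factor √(π/2) = 1.2533: SE = 0.204 × 1.2533 = 0.2557.

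**2. Attempt to reproduce 97% at 3 points.** A gap of D at the third assessment is a slope difference of D/2, so power = Φ((D/2)/SE − 1.96).
- D = 3: 1.5/0.2557 = 5.87; Φ(3.91) = 99.995%.
- D = 2.5: 99.8%.
- D = 2: 1/0.2557 = 3.91; Φ(1.95) = 97.4%.
- Difference giving exactly 97%: 2 × 0.2557 × (1.96 + 1.881) = 1.96 points.

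The printed figure is not reproduced at 3 points. For 97% power at 3 points this model needs only about 43 per arm.

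**3. Simulation of the described model.** Two separate simulations of the quantile random-intercept model agree with the closed form.
- At 3 points, one found 500 of 500 trials significant. The other found 150 of 150 under each of two quadrature settings, with empirical SE 0.243 to 0.245.
- At 2 points, the first gave 96.0% (empirical) to 97.5% (normal approximation). The second gave 98.2 to 98.3% in 300 samples.
- In a small run with a bootstrap SE in each sample, the mean SE was 0.255 and all 40 samples at 3 points were significant.

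**4. Simulation noise.** At 97% with 500 samples the Monte Carlo SE is √(0.97 × 0.03/500) = 0.76 percentage points. Even if true power were only 99.7%, 485 or fewer significant results out of 500 would have a probability below one in a billion.

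**5. Other readings, all at 3 points.**

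| Reading | Power |
|---|---|
| Endpoint-only comparison of medians, total SD √(2.95² + 2.04²) = 3.587 | 99.7% |
| Median change from baseline | 99.995% |
| Time in real months or weeks | 99.996% |
| 90 per arm | 99.98% |
| Random intercept ignored, mean slope | 98.7% |
| Random intercept ignored, median slope | 91.6% |
| 100 patients in total (50 per arm) | 98.6% |
| Time coded 1, 2, 3, no treatment main effect | 97.4% |

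One-sided testing would raise power further. Ignoring the random intercept, or using 100 patients in total, contradicts the text of 5.3. The last row does not.

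**6. The 1, 2, 3 coding.** With no treatment main effect, the gap between arms at each assessment is the code times the interaction coefficient. A 3-point gap at code 3 means a coefficient of 1. The SE is unchanged, so z = 1/0.2557 = 3.91 and power is 97.4%. The gap at baseline (code 1) is then 1 point, and the differential change is 3 − 1 = 2 points.

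**The case against.** The strongest reply is that nothing printed need be wrong. Section 5.3 defines the effect as a gap between arms at the primary endpoint, not as differential change from baseline, and it lists only an intercept and a time coefficient. With time coded 1, 2, 3 and no treatment main effect, the stated 97%, 3 points, 2.95 and 2.04 can all be exactly as run. This stands as a possible explanation that the text does not exclude. It does not rescue the statement as a reader will take it. In a randomised trial the arms are expected to be equal at baseline, so a 3-point endpoint difference is read as 3 points of treatment effect, whereas this coding tests 2.

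A second reply is that the protocol's Wald test relied on a standard error estimated in each sample by a method it does not name, whereas most of the results above rest on an empirical or normal-theory SE. This supports calling the 2-point figure approximate: with the simulated SEs, 97% falls nearer 1.9 points. It does not explain 97% at 3 points, which would need an SE inflated by about 53% (5.87/3.84 = 1.53).

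A third reply is that little depends on the figure. That is largely right. No interim analysis or decision rule uses it, and the result will be read from the estimate, its confidence interval and the p-value.

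**Conclusion.** The concern holds as a reporting error. On the printed inputs, with equal baselines and two-sided alpha 0.05, 100 per arm gives more than 99.9% power for 3 points, and about 97 to 98% power for roughly 2 points of differential change. The least favourable comparison tried that does not contradict 5.3 and starts the arms equal, the endpoint-only median test, still gives 99.7%. The cause may be the undeclared time coding, or a misreported power, difference or SD. The documents do not allow a choice between these.

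Three stronger inferences are not supported.
- A reader might infer that the trial is too small. If the SDs are right, the error is conservative and the trial has more power for 3 points than stated.
- A reader might solve backwards for the residual SD that makes 97% and 3 points agree (about 3.1) and conclude that the pilot SD was misprinted. Nothing in the documents supports that value, and the pilot data are not available.
- A reader might note that 220 × 0.9 = 198, not 200, and call the analysed sample misreported. Protocol 8.1 and SAP 4.7 include all randomised participants in a model that uses all available data, so 198 is not the number analysed, and a difference of that size hardly affects power.

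**What to change.** Re-run the section 5.3 simulation from the original code and reconcile the paragraph with it. State the codes of the time variable, the interaction coefficient, the treatment main effect assumed (zero or otherwise) and the sidedness. Then do one of two things:
- restate the result, which on the printed SDs would be above 99% power for 3 points and about 97% for about 2 points of differential change, to be confirmed by the re-run; or
- correct whichever input the re-run shows to be misprinted.

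The cost is one re-run and one reworded paragraph. Enrolment and the analysis plan stay as they are.

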### 5.4 INCLUSION AND EXCLUSION CRITERIA

#### 5.4.1 INCLUSION CRITERIA

- 1) Aged 9 to 17 years.
  - Confirmed by the caregiver and subsequently by the patient record system *TakeCare*.
- 2) A diagnosis of TD or Persistent (Chronic) Motor or Vocal Tic Disorder, based on the 5th edition of the Diagnostic and Statistical Manual of Mental Disorders [DSM-5; 32].
  - Confirmed by the assessor at the face-to-face or videoconference inclusion assessment.
- 3) A Total Tic Severity Score (TTSS) of >15 (or >10 if only motor or vocal tics, but not both, have been present the last week) on the YGTSS [YGTSS; 28].

- Confirmed by the assessor at the face-to-face or videoconference inclusion assessment.
- 4) A minimum of one available caregiver (parent) to support the child/adolescent throughout the treatment.
  - Confirmed by the caregiver at the telephone screening or/and face-to-face or videoconference inclusion assessment.
- 5) Regular access to a desktop or laptop computer connected to the internet, with the ability to receive e-mails, as well as a mobile phone to receive SMS (one of each is enough per family).
  - Confirmed by the caregiver at the telephone screening or/and face-to-face or videoconference inclusion assessment.

#### **5.4.2 EXCLUSION CRITERIA**

- 1) Previous behaviour therapy for tics, for a minimum of eight sessions with a qualified therapist within the 12 months prior to assessment.
  - Confirmed by the caregiver at the telephone screening or/and face-to-face or videoconference inclusion assessment.
- 2) Simultaneous psychological treatment for TD or Persistent (Chronic) Motor or Vocal Tic Disorder.
  - Confirmed by the caregiver at the telephone screening or/and face-to-face or videoconference inclusion assessment.
- 3) Initiation or adjustment of any psychotropic medication for TD or Persistent (Chronic) Motor or Vocal Tic Disorder within the eight weeks prior to assessment.
  - Confirmed by the caregiver at the telephone screening or/and face-to-face or videoconference inclusion assessment. Also followed up at each assessment point in the trial (except mid-treatment).
- 4) A diagnosis of organic brain disorder, intellectual disability, autism spectrum disorder, psychosis, bipolar disorder, anorexia nervosa, or alcohol/substance dependence.
  - Confirmed by the assessor at the telephone screening or/and face-to-face or videoconference inclusion assessment, with help of information from the caregiver and the child/adolescent, and the MINI-KID interview.
- 5) Immediate risk to self or others, requiring urgent medical attention, such as suicidality, or self-injurious tics.
  - Confirmed by the assessor at the telephone screening or/and face-to-face or videoconference inclusion assessment.
- 6) Child or caregiver (parent) not able to read and communicate in Swedish.
  - Confirmed by the caregiver or assessor at the telephone screening or/and face-to-face or videoconference inclusion assessment.

Related to above, it is not possible to be included into the trial if a potential participant has a close relationship to an already included participant (e.g. sibling, cousin), to avoid being

randomised into two different groups, with the risk of information “leaking” between the groups. This is important for the integrity of the controlled study design.

